### Study participants and inclusion criteria

Patients eligible for this project have to comply with all of the requirements below: are expected to be on warfarin treatment for the duration of at least 12 months, accept the study protocol and randomization, and sign an informed consent. Patients who fall into any of the following criteria are excluded in this project, including pregnancy or plan to get pregnant in 18 months, had experienced a bleeding complication requiring treatment in the past 6 months, are unable to attend a hospital in 6 hours, renal failure (hemodialysis or glomerular filtration rate < 10 mL/min), dementia or unstable psychiatric conditions or receiving treatment for cancer.

A patient who has been enrolled in the project will be considered as a dropout if meets any of the following criteria and the reason will be recorded: the patient decides to withdraw for any reason; the patient in the SMART model group does not follow the health-care professionals’ instruction for at least twice; the researcher considers the patient is no longer physically and/or psychologically fit to remain in the study. The impact of dropouts on statistical analyses, including intention to treat, will be used by carrying the last observation forward.

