#### Control patients

Patients will receive the warfarin education courses the same as the SMART model group after they sign the informed contents as mentioned above. However, we will not intervene the warfarin manage mode in the control groups.

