### Outcomes

#### Primary outcome measure

The difference in TTR between the SMART model group and the control group during the 12 month period of study.

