#### Data analyses

We will report continuous variables as means ± SD and categorical variables as proportions. Data will be checked for normal distribution by means of the Kolmogorov–Smirnov’s test. In compliance with the distribution of data, Student’s t-test or Mann–Whitney’s U-test will be used for comparisons between the SMART model group and control group. Chi-square or Fisher’s exact tests will be used to compare between the SMART model group and control group with respect to categorical data. The control of anticoagulation will be assessed by evaluating TTR with the Rosendaal method [18] in each arm. The follow-up assessment data will be analyzed using Generalized Linear Mixed Model and survival analysis. *P* ≤ 0.05 is considered statistically significant. All tests are two tailed. From the perspective of health-care payer, we will conduct a cost-effectiveness analysis to assess the economic impact of the SMART model for warfarin home management. A Markov model, a half-cycle correction and a discount of 5% will be constructed or used to estimate the total costs and quality-adjusted life-years (QALYs) over the 2-year period (the outcomes beyond the observation period will be predicted according to the results obtained in the study). We will collect the direct and indirect costs of each enrolled patient on warfarin, evaluate their quality of life through EQ-5D-3L utility value from data provided by patients, calculate QALYs, and analyze the effects of multiple variables by the Linear Mixed Effects Model. The direct costs include laboratory INR test fees in the control groups (or POCT fees in the SMART model group), outpatient clinic visit fees (or supervision fees in the SMART model group), hospitalization fees and emergency room visit fees. The indirect costs include deducted income due to absence of working, traffic fees and accommodation fees. Because warfarin is very cheap, the medication fee of warfarin is not calculated in each group. The incremental cost effectiveness ratio (ICER) will be calculated according to the total costs and QALYs, and one-way and probabilistic analyses will be performed to verify the stability of the model.

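### Repeated non-compliance makes a patient a dropout in the SMART arm only, and dropouts are filled by last observation carried forward, which can bias the 12-month TTR contrast in either direction

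*Protocol article*

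**What the plan says.** Study participants and inclusion criteria gives three reasons for counting an enrolled patient as a dropout. Two apply to every arm: "the patient decides to withdraw for any reason", and the researcher's judgement that the patient is no longer fit to remain. The third names one arm: "the patient in the SMART model group does not follow the health-care professionals’ instruction for at least twice". The paragraph closes with the handling rule: "The impact of dropouts on statistical analyses, including intention to treat, will be used by carrying the last observation forward".

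The primary outcome is "The difference in TTR between the SMART model group and the control group during the 12 month period of study". Under Data analyses, "The control of anticoagulation will be assessed by evaluating TTR with the Rosendaal method [18] in each arm". The same section adds: "The follow-up assessment data will be analyzed using Generalized Linear Mixed Model and survival analysis". It does not withdraw the carry-forward rule.

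For the control arms, the section Control patients states that "we will not intervene the warfarin manage mode in the control groups". Follow-up visits and data collection schedules all patients at months 3, 6, 9 and 12, but does not say whether this continues once a patient has been declared a dropout.

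**The concern.** Two features combine.

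- **A one-arm rule.** Whether patients follow remote instructions is part of what the SMART model is being tested on. A SMART patient who lapses twice becomes a dropout, and later TTR may be replaced by a carried value. A usual-care or anticoagulation-clinic patient who behaves in the same way stays in follow-up with the INRs actually observed. The two arms' means are then built differently for the same behaviour.
- **An imputation that does not fit the outcome.** TTR accumulates over time, and the Rosendaal method interpolates between measured INRs. Carrying a single INR forward makes every remaining day wholly in or wholly out of range. Carrying a period TTR forward ignores any later change.

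At stake is the primary between-arm contrast, planned around a 5-point difference. If INR results are not collected after dropout is declared, no later analysis can recover them, and the article reports that recruitment began in March 2021.

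**Working it through.** **The plan's own dropout figure.** Sample size determination starts from 31 patients per group and adds 10%: 31 × 1.10 = 34.1, which agrees with the stated 34 to rounding. The 10% is not split by arm, so the article gives no SMART-only excess. One has to be assumed.

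**Inputs from the article:** target difference 5 points; follow-up 12 months with contacts at months 3, 6, 9 and 12; planned dropout 10%.

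**Assumed inputs:** excess SMART dropouts *x* = 10% (5% and 20% as a range); dropout at month *t* = 3 or 6; true later TTR and carried value as given below.

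**Formula.** If a share *d* of an arm drops out at month *t*, and the carried value exceeds true later TTR by *e* points on average:

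shift in arm mean = *d* × (12 − *t*)/12 × *e*

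The bias in the contrast is the SMART shift minus the control shift. If *t* and *e* are the same in both arms, dropout common to both cancels and leaves *x* × (12 − *t*)/12 × *e*. If they differ, it cancels only in part.

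**Reading A: a period TTR is carried, and true later TTR is 10 to 20 points lower (*x* = 10%).**
- Month 6, 10 points: 0.10 × 0.50 × 10 = 0.5
- Month 3, 10 points: 0.10 × 0.75 × 10 = 0.75
- Month 6, 20 points: 0.10 × 0.50 × 20 = 1.0
- Month 3, 20 points: 0.10 × 0.75 × 20 = 1.5

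The range is 0.5 to 1.5 points. With *x* = 5% it is 0.25 to 0.75, and with *x* = 20% it is 1.0 to 3.0.

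**Reading B: a single INR is carried, and true TTR is 50% (*x* = 10%).** Here *e* is the percentage of last INRs in range minus 50.
- 80% or 20% in range, month 6: 0.10 × 0.50 × (±30) = ±1.5
- 80% or 20% in range, month 3: 0.10 × 0.75 × (±30) = ±2.25
- All or none in range, month 6: 0.10 × 0.50 × (±50) = ±2.5
- All or none in range, month 3: 0.10 × 0.75 × (±50) = ±3.75

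For one patient dropping out at month 3, TTR becomes 0.25 × 50 + 0.75 × 100 = 87.5 or 0.25 × 50 + 0 = 12.5, instead of 50.

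**When the bias vanishes.** Under either reading *e* = 0 gives zero bias. Under Reading B that means 50% of last INRs in range when true later TTR is 50%.

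**The case against.** The best defence has four parts.

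- **Dropouts are not removed.** The handling sentence names intention to treat, so these patients remain in their randomised arm. That is correct. The problem is which values represent them.
- **The asymmetry has a structural cause.** The study gives controls no warfarin-management instructions, so a matching criterion would be hard to write. This explains the rule but does not neutralise its effect on the comparison.
- **The mixed model might take over.** It is named for follow-up data, but nothing says that it replaces carrying forward. If it is fitted to filled-in data, it loses the advantage of using observed data under missing-at-random.
- **An analysis plan may add detail.** It may, but the article states both the one-arm rule and LOCF outright, so this is not a matter of omission.

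A reader might infer several stronger claims that the article does not support:

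- **That observation certainly stops when SMART fails.** The article is silent on this, and its follow-up schedule covers all patients.
- **That the bias favours SMART.** It would if the carried value predates a deterioration. If the last INR is out of range when the patient is classed as a dropout, carrying it forward penalises SMART.
- **That ±3.75 points is the expected size.** It needs every excess dropout at month 3 and every last INR on the same side of the range.
- **That LOCF is always biased or always understates the standard error.** With stable TTR and unrelated dropout, the expected bias is zero. Values such as 87.5 and 12.5 can widen the spread between patients.

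**Conclusion.** The point holds as a structural fault. As written, a non-compliance criterion in one arm feeds an imputation rule that does not suit a 12-month TTR, and the primary contrast can be biased. Neither direction nor size can be determined from the article, because it states neither the SMART-only excess nor which quantity is carried.

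Under the assumed 10% excess, the plausible shifts of about 0.5 to 2.25 points are 10% to 45% of the 5-point target (0.5/5 and 2.25/5). The extreme of 3.75 is 75% of it. Dropout common to both arms partly cancels and should not be counted. The fault deserves correction because the shift can be a material share of the target and because lost INRs cannot be recovered later.

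**What to change.** 1. **Retain the data.** State that meeting the non-compliance criterion does not end outcome data collection. Record it as non-adherence, continue the existing month 3, 6, 9 and 12 collection of INR results, and use those observed data in the arm as randomised. Whether home testing continues is a clinical matter for the investigators, and this change does not touch it.
2. **Replace LOCF.** Compute TTR only over days bracketed by INR results. Analyse the repeated TTRs with the mixed model already planned, fitted to observed and not filled-in data. Add a multiple-imputation sensitivity analysis with delta adjustment, because non-adherers' unobserved TTR may differ from what missing-at-random predicts.

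**Cost.** Protocol wording and modest programming; contacts stay on the existing schedule. Some usual-care patients may have few INRs in a 3-month period, so their period TTRs will be imprecise or unavailable. The estimated effect may also turn out smaller.

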In China, the percentage of time in therapeutic range (TTR, a tool of measuring warfarin treatment effects) was less than 40%, which was significantly lower than that of 62% in western countries [4]. Clinical observation studies found that warfarin associated ischemic stroke and intracranial bleeding were respectively 5.23 and 2.94% in patients from China, significantly higher than patients from the rest of the world (2.94 and 0.63%, respectively) [5]. In warfarin-treated patients in China, the median in-hospital direct cost per patient was about $3, 000 for thrombosis and $4, 500 for intracranial hemorrhage [6]. These data suggest that warfarin management in China needs further improvement. An investigation study launched by the PI using the Andersen’s Health Services Utilization Behavioral Model in 469 patients on warfarin indicated that long time and high cost for travel, low family income, low quality of warfarin monitoring and dosing in local hospitals were dominant reasons for missing follow-ups (data not published yet).

Anticoagulation clinics (AC) have been proved safer and more effective than usual care in warfarin management [7, 8], but there are only about 50 ACs located in big cities of China (mainly run in a physician-pharmacist cooperative AC pattern) at present. The number of ACs is too low, and it is not easy to open more ACs due to limitation of health care professionals and longtime education.

Point-of-care testing (POCT) device designed for measuring INR by patients or their families was first developed in 1980s in America [9] and then widely used in many developed countries. Compared to traditional laboratory INR test in outpatient clinics, POCT has great advantages in convenient home testing and fast result reporting. Soon patient self-testing (PST) for warfarin home management by using POCT devices and telehealth has been rapidly applied in developed countries. Although the PST model of warfarin management has demonstrated improvement of clinical outcomes compared to usual care clinics and anticoagulation clinics [10], it is rarely applied in developing countries, including China.

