#### Follow-up visits and data collection

Each of the enrolled patients has to record his/her warfarin related information in a printed monitoring handbook, including INR results, warfarin dosage, other medicine, diet change, new disease, and thrombosis or bleeding events (if occurs). All the patients are required to receive follow-ups at the 3rd, 6th, 9th and 12th month through outpatient clinic visits, telephone or online interviews. At each follow-up time-point, the research stuff will collect the warfarin related information. Double data entry will be carried out to ensure data accuracy and data will be kept in encrypted mobile hard disks to protect patients’ privacy. Only the corresponding author has access to the final trial dataset. As shown in Table 3, patients are required to provide the information of warfarin dosage and INR results, the numbers of going to the outpatient clinics or inpatient treatment due to warfarin, quality of life as measured by the health index scale (EQ-5D-3L) [16], and the related treatment costs. At baseline and the last time visit, patients are required to fill in the Morisky anticoagulant compliance questionnaire [14] and the oral anticoagulation knowledge test [15]. An anticoagulation satisfaction survey by using the Duke Anticoagulation Satisfaction Scale [17] will be conducted to all the patients at the end of the study. The research staff will send text messages to remind the patients for follow-ups and all the participated patients will receive certain amount of compensation fees to sustain their involvement in the study.

**Table 3 Tab3:** Measurement domains, survey methods and collection time-points

Variable	Component	Measurement methods	Baseline	3rd M	6th M	9th M	12th M
**Socio-demographic parameters**	Gender, age, telephone, address, education, occupation and annual income	Face-to-face interview	√				
**Clinical parameters**	Height, weight, warfarin indication, start date of warfarin, warfarin dosage, TTR calculated by INR tests in the preceding 12 months, history of thrombosis or major bleeding, concomitant diseases and medicine Warfarin dosage, INR, bleeding or thrombosis, other clinical adverse events	Face-to-face interview	√				
		Face-to-face interview, telephone or online interview		√	√	√	√
**Behaviour parameters**	Anticoagulant compliance, warfarin knowledge,	Morisky Anticoagulant Compliance Questionnaire [14], Oral Anticoagulation Knowledge (OAK) Test [15]	√				√

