	Treatment behavior, quality of life	Self-made questionnaire, EQ-5D-3L Form [16]	√	√	√	√	√
	Anticoagulation satisfaction	Duke Anticoagulation Satisfaction Scale [17]					√
**Economic parameters**	Direct costs (INR test fees, outpatient clinic visit fees, hospitalization or emergency room visit fees if occurs), Indirect costs (deducted income due to absence of working, traffic and accommodation fees)	Face-to-face interview, telephone or online interview	√	√	√	√	√

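### Last observation carried forward, stated without exception, does not suit interval costs: it can repeat a one-off admission or extend a quiet quarter, and it biases mean cost when dropout follows events

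*Protocol article*

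**What the plan says.** Under Study participants and inclusion criteria, the protocol article gives one rule for dropouts: "The impact of dropouts on statistical analyses, including intention to treat, will be used by carrying the last observation forward". The same section lists three ways to become a dropout: withdrawal for any reason; for SMART patients only, failing at least twice to follow staff instructions; and the case where "the researcher considers the patient is no longer physically and/or psychologically fit to remain in the study". Death is not on that list. It appears under Secondary outcome measures as an event.

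Under Follow-up visits and data collection, "All the patients are required to receive follow-ups at the 3rd, 6th, 9th and 12th month". Table 3 schedules the economic items at baseline and at each of those visits. Direct costs include "hospitalization or emergency room visit fees if occurs"; indirect costs include lost income, travel and accommodation. EQ-5D-3L is collected at the same times.

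Under Data analyses, "We will collect the direct and indirect costs of each enrolled patient on warfarin". The ICER is formed from total costs and QALYs, estimated with a two-year Markov model that projects beyond the observed year from the trial's own results. Mixed models are named for the follow-up data and again in the sentence on costs and QALYs. Nothing says whether they replace carry-forward or are fitted to data already filled by it.

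**The concern.** Carry-forward assumes that a quantity stays where it was last seen. For a state such as EQ-5D-3L that is doubtful but coherent. A cost for an interval is a flow. Carrying it forward asserts that the same spending happened again: a patient admitted once and then lost is charged for a new admission each quarter, and a patient lost after a quiet quarter is recorded as having no further admissions.

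The dropout criteria make it plausible that these errors do not balance. A stroke or intracranial bleed could lead to a patient being judged unfit to continue. Non-adherence removes patients from the SMART arm only. The arms are also costed differently (home-test and supervision fees in SMART, laboratory and clinic fees in controls), so a SMART patient removed for non-adherence would keep SMART-type routine costs even if, as one may infer, that patient went back to clinic care.

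Cost is a secondary outcome and one of the two inputs to the ICER, and the Discussion makes wider use of the model depend on cost-effectiveness.

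**Working it through.** **The plan's own figure.** The document gives no cost, QALY or ICER result to reproduce. Its only figure that uses dropout is the sample-size allowance: 31 × 1.10 = 34.1, given as 34. The 10% is used below.

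**Inputs from the protocol.** Four post-baseline visits, hence four quarters; arms of 360 (SMART, usual care) and 120 (anticoagulation clinic); 10% dropout; and, from Background, "the median in-hospital direct cost per patient was about $3, 000 for thrombosis and $4, 500 for intracranial hemorrhage" and an intracranial bleeding figure of 2.94%.

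**Assumptions.** Each record covers the interval since the last visit. The 2.94% is a 12-month risk (no time base is given), spread evenly, so 0.735% per quarter. The median cost stands in for a mean.

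**Step 1: one patient.** If the admission, costing C, falls in the last observed quarter q, the total under carry-forward is C × (1 + 4 − q) and the excess is C × (4 − q).

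| Last seen | Total, C = $3,000 | Total, C = $4,500 | Excess |
|---|---|---|---|
| Month 3 | $12,000 | $18,000 | $9,000 / $13,500 |
| Month 6 | $9,000 | $13,500 | $6,000 / $9,000 |
| Month 9 | $6,000 | $9,000 | $3,000 / $4,500 |

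The admission is charged 2 to 4 times. One patient with the largest excess moves the mean of a 360-patient arm by 13,500 / 360 = $37.50, and of the 120-patient arm by 13,500 / 120 = $112.50.

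**Step 2: quiet quarters.** If a share d of an arm leaves after event-free quarters, spread evenly over the year, the mean number of unfilled quarters is (3 + 2 + 1 + 0) / 4 = 1.5. The event cost lost is d × 1.5 / 4: 3.75% at d = 10% and 11.25% at d = 30%.

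**Step 3: both together.** True mean admission cost is 0.0294 × 4,500 = $132.30 per patient, or $33.075 per quarter. For 10% dropout over the three gaps between visits, the chance of leaving after a quarter is h = 1 − 0.9^(1/3) = 0.0345. Let it be m times higher after a quarter with an admission. Repeats add, and carried zeros remove, so approximately

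net error = 33.075 × h × [3 + 2(1 − h) + (1 − h)²] × (m − 1) = 33.075 × 0.0345 × 5.863 × (m − 1) ≈ $6.69 × (m − 1).

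A simulation (360 per arm, 4,000 runs) agrees:

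| m | Chance of leaving after admission | Formula: mean under carry-forward | Simulated: true mean | Simulated: carry-forward mean | SD of arm mean, true / carry-forward |
|---|---|---|---|---|---|
| 1 | 3.5% | $132 | $133 | $133 | $41 / $44 |
| 5 | 17% | $159 | $132 | $159 | $41 / $59 |
| 10 | 35% | $193 | $132 | $192 | $41 / $72 |

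At m = 1 the mean does not move and only its spread grows slightly. At m = 5 and m = 10 it rises by about 20% and 45%. If dropout is instead concentrated among event-free patients, the error is negative, as in Step 2.

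**The case against.** Several points on the other side stand.

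- **No recall period is stated.** Patients also keep a running handbook. If the recorded costs were cumulative, carry-forward would freeze a total and repeat nothing. The per-interval reading is the natural one for costs asked about at each visit, but it is an inference.
- **Bias needs informative dropout.** With m = 1 the mean is unaffected. The multipliers of 5 and 10 have no source in the document. A patient who leaves before the admission is recorded has no admission to carry forward.
- **The route to the ICER is unclear.** The Markov model's inputs are not described, and mixed models can use incomplete follow-up without filling it. About 90% of patients are expected to be fully observed. A reader might infer that the ICER as a whole rests on costs and QALYs that never occurred; the document does not support that.
- **Death.** A reader might infer that a living utility is carried past death. With assumed utilities of 0.6 to 0.9 over 0.25 to 0.75 year, that would add 0.15 to 0.68 QALY per affected patient. But carry-forward is tied to dropouts, death is not a dropout criterion, and nothing says utilities continue after a recorded death. This is a point to clarify, not a stated rule.

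What does not stand is the suggestion that this is only detail left to the analysis plan. The rule is written down, covers the statistical analyses without exception, and is the only dropout rule given. Naming mixed models does not cure it, since models fitted to filled-in data inherit the error.

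**Conclusion.** The point holds in a limited form. As written, the carry-forward rule is wrong for episodic costs. On the per-interval reading it multiplies an admission in a dropout's last observed quarter by 2 to 4 (excess $3,000 to $13,500 per affected patient) and treats patients lost after a quiet quarter as event-free.

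The direction of error in an arm mean is not fixed. It is roughly zero when dropout is unrelated to events, upward when dropout follows admissions (about 20% to 45% of mean admission cost in the assumed scenarios), and downward when event-free patients leave. The SMART-only non-adherence criterion makes unequal error between arms plausible, but this has not been shown. No between-arm cost difference or ICER effect can be computed from the document; the error can reach both if filled totals feed them.

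**What to change.** State in the analysis plan that last observation carried forward is not used for costs, for visit and admission counts, or for utilities and QALYs. Keep observed quarters as observed. Handle missing quarters under missing at random, either by multiple imputation within arm (for example from hospital, baseline cost and the observed quarters) or by inverse-probability-weighted interval costs, and show a complete-case result as a sensitivity analysis. State the period that each cost record covers and how the named mixed models relate to the dropout rule. As a clarification only, count utility as 0 after a recorded death.

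This takes about a paragraph of wording and modest extra analysis, with no new data. Intervals may be wider because they reflect the cost data that are actually missing.
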